| Inclusion and Exclusion Criteria | Inclusion criteria   - 20 years of age or older - Confirmed diagnosis of type 2 diabetes made within past 6 months - Willing to return for all follow up visits (3, 6, 9, 12 months after baseline visit)   Exclusion criteria  To help ensure sufficient rate of return for follow up in the longitudinal study, the exclusion criteria are the following:   - Patients who are currently pregnant or are breast feeding, or plan to get pregnant during the following year; - Patients who are not willing or not able to return to the same hospital for follow up visits every 3 months for one year after enrollment; - Patients who are participating in any other interventional clinical trials; - Patients who have been on diabetes medications but have no clear information regarding the medication used; - Patients who are not willing to sign informed consent form. |
| Observational endpoints | **Primary endpoint**  The overall proportion of patients whose HbA1c is less than 7%, measured at the end of one year follow up.  **Secondary endpoints**   1. The proportions of patients receiving one OAD, two OADs, > two OADs, insulin alone, insulin+one OAD, insulin+two OADs, insulin+>two OADs and by class of OADs at 3, 6, 9, and 12 months; 2. Mean duration of diet & exercise alone (t4), initial anti-diabetic treatment (ADT) (t1), initial ADT is switched or 2nd ADT is added (t2), 2nd ADT is switched or 3rd ADT is added (t3) ; (Figure 1 Treatment Pattern Diagram); 3. The proportion of patients reached the therapeutic target of glycemic control by treatment regimen and by OAD class at 3, 6, 9 and 12 months: 4. The correlation between treatment patterns and patient demographics, social-economic status, insurance, medical history, HbA1C level, type of hospital, physician years of practice, etc; 5. Incidence of microvasular diabetic complication: diabetic retinopathy, nephropathy, neuropathy, and macrovascular complications: cardiovascular events, peripheral vascular complications, and stroke, at 3, 6, 9, and 12 months; 6. Were the diabetes related clinical examinations applied such as Fundus examination and diabetic foot screening; 7. Incidence of hypoglycemia associated with various ADTs; 8. Diagnosis patterns, including the methods of diagnosis (i.e. routine physical examination, seeing doctors for other diseases, etc), and type of hospital, as well as its association with demographics and regions of residence. |

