# STUDY DESIGN

## General design

Any newly diagnosed (within 6 months) type 2 diabetic patient who is visiting tier 3, 2, or 1 hospitals, may be considered for enrollment in this study, as long as the patient meets the inclusion and exclusion criteria and is willing to sign on the informed consent form.

Enrolled patients will receive routine treatment (diet & exercise or medication) and will be asked to return to the same investigator for follow up visits at 3, 6, 9 and 12 month after the baseline visit.

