## Secondary endpoints

The secondary endpoints of this study include the following;

1. The proportions of patients receiving one OAD, two OADs, > two OADs, insulin alone, insulin+one OAD, insulin+two OADs, insulin+>two OADs and by class of OADs at 3, 6, 9, and 12 months;
2. Mean duration of diet & exercise alone (t_4_), initial anti-diabetic treatment (ADT) (t_1_), initial ADT is switched or 2^nd^  ADT is added (t_2_), 2^nd^ ADT is switched or 3^rd^ ADT is added (t_3_) ; (Figure 1 Treatment Pattern Diagram);
3. The proportion of patients reached the therapeutic target of glycemic control by treatment regimen and by OAD class at 3, 6, 9 and 12 months:
4. The correlation between treatment patterns and patient demographics, social-economic status, insurance, medical history, HbA1C level, type of hospital, physician years of practice, etc;
5. Incidence of microvasular diabetic complication: diabetic retinopathy, nephropathy, neuropathy, and macrovascular complications: cardiovascular events, peripheral vascular complications, and stroke, at 3, 6, 9, and 12 months;
6. Were the diabetes related clinical examinations applied such as Fundus examination and diabetic foot screening;
7. Incidence of hypoglycemia associated with various ADTs;
8. Diagnosis pattern: to assess the methods of diagnosis (i.e. routine physical examination, seeing doctors for other diseases, etc), and location of diagnosis, demographic information of the patients and the regions of residence;
9. Quality of life assessment (baseline and the last visit);
10. Resource consumption patterns based on the information collected on the cost of medications, cost of diagnostic test and other relevant [procedure.

Figure 1 Treatment Pattern Diagram

[figure not shown]

T1 = duration between diagnosis and initiation of (single) treatment regime， T2 = duration between initiation of single treatment regime and duple regime， T3 = duration between initiation of duple treatment regime and multiple regime

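### The treatment-step durations in secondary endpoint item 2 do not match the Figure 1 legend, and they are summarised by a mean that unfinished durations bias downward

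*Protocol*

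**What the plan says.** Item 2 of section 6.2 defines the durations as "Mean duration of diet & exercise alone (t_4_), initial anti-diabetic treatment (ADT) (t_1"), followed by a step labelled t2, described with "initial ADT is switched or 2^nd" ADT being added, and a third, "2^nd^ ADT is switched or 3^rd^ ADT is added (t_3"). The synopsis carries the same list: "Mean duration of diet & exercise alone (t4), initial anti-diabetic treatment (ADT) (t1), initial ADT is switched or 2nd ADT is added (t2"). Both refer the reader to Figure 1.

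The legend under Figure 1 gives three definitions: "T1 = duration between diagnosis and initiation of (single) treatment regime"; "T2 = duration between initiation of single treatment regime and duple regime"; and "T3 = duration between initiation of duple treatment regime and multiple regime". It mentions neither switches nor a fourth interval. The diagram itself is not reproduced in the text available for review.

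Section 4.1 sets "follow up visits at 3, 6, 9 and 12 month after the baseline visit". Section 7 assumes attrition of about 20%, citing a range of 14% to 25%. The time-to-event option it names (Cox or logistic regression) is for inadequate glycemic control, not for these durations.

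**The concern.** Item 2 and the legend are meant to describe the same intervals, but an analyst who follows one will report something different from an analyst who follows the other, under the same label. A statistical analysis plan cannot settle this by adding detail, because the protocol gives two definitions and does not say which governs.

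The second problem is the summary measure. A mean duration needs every duration to be complete. Here some patients will still be on their regimen at month 12 and others will be lost before then. Averaging only completed durations keeps the fast changers; treating unfinished durations as complete counts them as shorter than they are. Both errors pull the mean down.

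The evolution of treatment patterns is the first half of the primary objective, and item 2 is the only listed endpoint that measures when treatment steps occur.

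**Working it through.** **Definitions.** Take a hypothetical patient: diagnosis at month 0, diet and exercise only until month 4, first drug at month 4, second drug added at month 10.

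| Interval | Item 2, plain reading | Figure 1 legend |
|---|---|---|
| Month 0 to 4 (4 months) | t4 = 4 | T1 = 4 |
| Month 4 to 10 (10 − 4 = 6 months) | t1 = 6 | T2 = 6 |
| From month 10 | t2, open | T3, open |

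The same patient has t1 = 6 and T1 = 4. For a patient first managed without drugs, the legend's labels are shifted by one step.

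Now let the first drug be replaced, not supplemented, at month 10. Under item 2 the step that began at month 4 closes after 6 months. Under the legend T2 stays open, because the patient is still on a single regimen.

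**Mean duration.** The protocol states no expected duration and no rate of treatment change, so there is no figure of its own to reproduce. The sample size (1,315 × 3 = 3,945; 3,945 / 0.80 = 4,931) rests on the proportion at HbA1c target and does not use these durations.

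Assumptions for illustration only: the time to the next step is exponential, every patient starts the interval at month 0, follow-up to month 12 is complete, and a share q changes by month 12.

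- Rate: λ = −ln(1 − q) / 12
- True mean: 1 / λ
- Mean with the rest cut at 12: R = q / λ
- Mean among changers only: (R − 12(1 − q)) / q

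For q = 0.50: λ = 0.6931 / 12 = 0.05776; true mean 17.3; R = 0.50 / 0.05776 = 8.66; changers (8.66 − 6) / 0.50 = 5.3.

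For q = 0.90: λ = 2.3026 / 12 = 0.1919; true mean 5.2; R = 0.90 / 0.1919 = 4.69; changers (4.69 − 1.2) / 0.90 = 3.9.

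| Share changing by month 12 | Changers only | Rest cut at 12 | True mean |
|---|---|---|---|
| 20% | 5.8 | 10.8 | 53.8 |
| 30% | 5.6 | 10.1 | 33.6 |
| 50% | 5.3 | 8.7 | 17.3 |
| 70% | 4.8 | 7.0 | 10.0 |
| 90% | 3.9 | 4.7 | 5.2 |

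All values are in months. From 20% to 50% changing, the true mean falls by a factor of 53.8 / 17.3 = 3.1, while the mean among changers moves only from 5.8 to 5.3. At 90% the gap is small.

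With no loss to follow-up, the third column is a valid 12-month restricted mean. It misleads only when presented as the mean duration. If patients lost early are counted as complete, it falls below even that.

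**The case against.** Item 2 can be read as the time until each event, since its wording for t2 and t3 names events, not regimens. Then t1 is time to the first drug, as in the legend, and t2 comes close to the legend's T2. This is a fair reading and it removes the 6-against-4 discrepancy. It also makes t1 overlap with t4, and it leaves the switch conflict untouched.

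The protocol names a mean but no estimator, and rules for unfinished durations often sit in a statistical analysis plan, which is not shown. So the absence of a censoring rule is not held against the protocol. A restricted mean would even be compatible with the present wording. What stands is that the protocol fixes an unqualified mean as the endpoint, and over 12 months that quantity cannot be estimated without a model.

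A reader might go further in three ways that the documents do not support:

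- That most durations are cut off at month 12. No rate of change is given. The legend's T1 starts at diagnosis, up to 6 months before baseline, and patients already on drugs may enrol if their drug information is clear, so many T1 values may be complete at entry.
- That t4 also has two definitions. It appears only in item 2, and the diagram, which might show it, is not available.
- That the treatment-pattern results as a whole would be wrong. The regimen proportions at 3, 6, 9 and 12 months (item 1) and target attainment by regimen (item 3) do not use these intervals.

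**Conclusion.** The point holds, limited to item 2. Whether a switch ends a step is contradictory on any reading; what t1 measures is contradictory on the plain reading and ambiguous otherwise. This needs no numerical assumption.

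The downward bias of an ordinary mean is certain in direction wherever unfinished durations exist. Its size is not known from the protocol. Under the constant-rate illustration it runs from large (5.3 or 8.7 months against 17.3 with half the patients changing) to small (3.9 or 4.7 against 5.2 with 90% changing).

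The primary endpoint and the sample size are unaffected. This should be corrected before the durations are analysed.

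**What to change.** 1. Use one set of definitions in the synopsis, section 6.2 and Figure 1, with a start event and an end event for each of t1 to t4. State explicitly whether a one-for-one switch ends a step.
2. Replace the unqualified mean by Kaplan-Meier estimates with unfinished durations censored at the last visit, and report a restricted mean over a stated horizon. State the time origin with it: an interval counted from diagnosis can extend to about 6 + 12 = 18 months, one counted from baseline to about 12.
3. Confirm that the eCRF captures start and change dates of anti-diabetic drugs. Section 5.2 lists drug names, dosage, frequency, years taken, purpose and changes since the last recorded visit, but not dates explicitly.

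Items 1 and 2 cost only wording. Item 3 is a check. If dates are not collected, either a data field must be added or changes can be placed only between two visits, which are 3 months apart, and the analysis must allow for that. It should therefore not be assumed that the repair is wording alone.

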## Secondary Objectives:

1. To evaluate the reasons and the process of each step of the changes in treatment regimen during the 12-month follow up.
2. To evaluate the influential factors related to the changes of the treatment patterns for newly diagnosed T2D, including clinical outcomes, pattern of blood glucose monitoring, social-economical status (i.e. insurance status, income status, education background, etc), patients’ compliances, patients’ knowledge of diabetes, hospital tier, specialties of the physicians;
3. To assess the incidence of CVD risk factors (i.e. hypertension, lipidemia and obesity) and the intervention patterns;
4. To assess the associated incidence of diabetic complications, including cardiovascular / cerebrovascular and microvascular diseases;
5. To assess the application of diabetes related clinical examinations such as Fundus examination and diabetic foot screening;
6. To assess the methods of diagnosis (i.e. routine physical examination, health screening, seeking health care due toT2D symptoms, seeing doctors for other diseases, etc), and location of diagnosis (i.e. the tier of hospital, the physician specialty, etc) and the influential factors.
7. To assess the incidence of hypoglycemia and other AEs and SAE, that may be related to anti-diabetes medications.
8. To access the medical resource consumption pattern for treating diabetes.
9. To evaluate the health conditions and quality of life at the baseline and at the 12th month.

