## Exclusion criteria

- Patients who are currently pregnant or are breast feeding, or plan to get pregnant during the following year;
- Patients who are not willing or not able to return to the same hospital for follow up visits every 3 months for one year after enrollment (e.g. do no reside locally);
- Patients who are participating in another interventional clinical trials;
- Patients who have been on diabetes medications but have no clear information for the drugs used;
- Patients who are not willing to sign informed consent form.

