## Measurements at Baseline and Follow-up Visits

Each patient will return to see the same physicians for follow up visits at 3, 6. 9 and 12 month after the first visit, and the following measurements will be recorded, laboratory reports will be obtained.

- Blood pressure: The subjects should be resting for at least 5 minutes prior to measurement of blood pressure. Measure the sitting or supine blood pressure, and take the mean of values of 2 continuous measurements. There should be 2 minutes interval between the 2 measurements.
- Height and body weight: Remove the shoes and socks prior to measurement, as well as wear light clothes. Formula for body mass index calculation: BMI= Body weight (kg)/Body height^2^ (m)
- Waist circumference: Remove the clothes on the waist and stand relaxed with both hands down naturally. Then use tape around the waist and adjust its location to make the tape pass the intermediate points between superior margins of hip bones at both sides and lower costal margins. Pay attention to that the tape should be parallel to the floor and cling to but no compress the skin.
- Health behavior
- Smoking history: Record the average number of cigarettes per day and smoking time. A smoker is defined as a person who smokes 1 cigarette a day on the average for at least 1 year.
- Exercise pattern: Physical inactivity means the subjects do not have frequent physical exercise (such as amount of exercise equal to that in walking for at least 20-30 minutes a day, 3-4 days a week).
- Medication: Including medication previously prescribed for glycemic control and any other concurrent medications. Record generic name, brand name, dosage, frequency, years taken, and purpose. Current and any change of medications since last recorded visit for treatment of type 2 diabetes, diabetic complications, lipid-regulation, and hypertension, including prescription drugs, OTC drugs and Chinese herbal medicines should be recorded.
- Reason for adjusting anti-diabetic medications
  1. Unsatisfactory treatment outcomes: according to FBG results, or 2-hour postprandial blood glucose, or HbA1c
  2. Adverse events: hypoglycemia, gastrointestinal reactions, edema, weight gain, change of liver or kidney functions, allergic, other discomforts.
  3. Economical reasons
  4. Self-adjustment: details will be required
- Compliances: does the patient routinely take medicines in accordance with the prescriptions, if not, the specific reasons will be required

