- Hypoglycemic symptoms and severity: Hypoglycemia is defined as the fasting plasma glucose level below 70 mg/dL according to the American Diabetes Association 2009 Position Statement [12]. The symptoms of hypoglycemia include but not limited to sweating, hunger, trembling, anxiety, confusion, blurred Vision. A simple questionnaire will be used to record patient reported symptoms and severity.
- Lab tests: Blood tests should be performed after fasting for at least 10 hours.
- Serum glucose: The oxidase method should be used;
- HbA1C: It should be determined by high performance liquid chromatography (HPLC)
- Lipid panel: TC – total cholesterol, LDL-C – low density lipoprotein, TG – triglyceride, HDL-C – high density lipoprotein
- Kidney function: serum creatinine
- Liver function (Gamma-GT, ALT, AST)
- Urine test (urine albumin, creatinine or albumin / urine creatinine ratio)

Notice: Lipid panel and liver function are tested every 6 months, while other lab tests are conducted every 3 months.

If any additional diagnose test is ordered as part of the routine medical course, a copy of the results should be obtained. Any change of medical history, hospitalization, and medication will be specially noted (cause, dosage, outcome, etc). Unsolicited safety reports on products marketed by Bristol Myers Squibb will be collected.

Lab test methods:

- - - All blood samples should be venous blood after at least10-hour fasting;
    - HbA1c should be tested using high performance liquid chromatography (HPLC) method;
    - Fasting blood lipids: total cholesterol, triglycerides, high density lipoprotein, low density lipoprotein;
    - Urinalysis: 24 hours urine, short time urine, or random urine are accepted;
    - Albumin to creatinine ratio: urine (3-4 ml) measured within two hours after collection. Urine albumin is tested using immune turbidimetric method. Urine creatinine is tested using oxidase method.
- In addition to the scheduled follow-up visits of NEW2D and the information collected at each visit, the extra visits of the patients should also be briefly recorded, including the date, the reason (needed prescription, needed treatment), having tested for blood glucose, method of the test and the results if available;
- Adverse events: gastrointestinal reactions, edema, weight gain, change of liver or kidney functions, allergic, other discomforts (details);
- Severe adverse events: for BMS products only.

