# INFORMED CONSENT

The subjects (or legal representatives of the subject) should sign the informed consent form on the first visit after fully understand of the purpose and procedure of the study. The patients should be aware that they should return for follow up visits every 3 months for one year for physical and laboratory evaluations.

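### Endpoint 10's diagnostic-test cost is in large part set by the protocol's own laboratory schedule, so a total that includes it is not usual-care resource use

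*Protocol*

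**What the plan says.** Secondary objective 8 (Protocol, 3.2) reads "To access the medical resource consumption pattern for treating diabetes". The matching endpoint, 6.2 item 10, is "Resource consumption patterns based on the information collected on the cost of medications, cost of diagnostic test and other relevant" procedures. The general design (4.1) leaves treatment to routine practice.

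Testing is not left to routine practice. Section 5.2 says "Lipid panel and liver function are tested every 6 months, while other lab tests are conducted every 3 months", and the flow chart in 5.3 repeats this. The tests sit on fixed visits: "Each patient will return to see the same physicians for follow up visits at 3, 6. 9 and 12 month after the first visit". Attendance is a condition of entry, since section 4.3 excludes anyone "not willing or not able to return to the same hospital for follow up visits every 3 months for one year after enrollment". Section 8 has patients told at consent that "they should return for follow up visits every 3 months for one year for physical and laboratory evaluations".

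Section 5.2 also covers testing beyond the schedule: "If any additional diagnose test is ordered as part of the routine medical course, a copy of the results should be obtained". Extra visits are to be recorded briefly, with date, reason and any glucose test. Item 10 does not use this distinction between scheduled and additional tests.

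**The concern.** An observational study can describe resource use only to the extent that it does not create it. Here the protocol orders a set of laboratory tests for every patient and then takes the cost of diagnostic tests as part of the resource pattern. A patient whose physician would have ordered none of these tests in the year carries the same scheduled cost as one whose physician would have ordered all of them.

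What is at stake is the reading of one secondary endpoint. A single cost total would be taken as what it costs to treat newly diagnosed patients in Chinese hospitals, while its test component has a floor set by the study.

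**Working it through.** The protocol gives no figure for endpoint 10, so there is none to reproduce. The check counts what the schedule fixes and then asks what can be concluded from it.

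**Inputs** (Protocol 5.2 and 5.3)
- Every 3 months: glucose, HbA1c, creatinine, urine (4 panels).
- Every 6 months: lipids, liver function (2 panels).
- Visits at baseline and months 3, 6, 9 and 12. I take the 6-monthly panels as months 0, 6 and 12.

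**Step 1: scheduled panels per completer**
- Follow-up: 4 × 4 + 2 × 2 = 20.
- With baseline: 4 × 5 + 2 × 3 = 26.

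**Step 2: scheduled share of follow-up panels**

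Let x be the number of unscheduled panels per patient in the year. The documents do not give x, so a range is assumed. Share = 20 / (20 + x).
- x = 0: 100%
- x = 5: 20/25 = 80%
- x = 10: 20/30 = 67%
- x = 20: 20/40 = 50%
- x = 40: 20/60 = 33%

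The schedule supplies at least half of the panels unless x exceeds 20. These are shares of counts. They equal shares of cost only if panels cost about the same.

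**Step 3: what the recorded data can say about usual care**

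Let S be the cost of scheduled tests, A the cost of additional routinely ordered tests, and f (from 0 to 1) the fraction of S that would have been ordered anyway. Usual-care test cost is U = A + fS.
- Total with scheduled tests: A + S, which overstates U by (1 − f)S.
- Total without them: A, which understates U by fS.

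The protocol specifies nothing that reveals f. A physician who would have ordered exactly the scheduled tests (f = 1) and one who would have ordered none (f = 0) both show 20 scheduled and 0 additional panels. The two totals therefore bracket U but do not locate it. The bracket assumes that additional tests are fully recorded and were not themselves prompted by a scheduled result.

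**Step 4: the endpoint as a whole**

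Let m be the medication share of total cost, which the documents do not give. Suppose scheduled tests are 80% of non-drug cost (an assumption). The schedule-driven share of the total is then 0.8 × (1 − m):
- m = 0: 80%
- m = 0.25: 60%
- m = 0.50: 40%
- m = 0.75: 20%

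The documents do not settle where in this range the endpoint falls.

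**The case against.** The strongest reply is that this is a costing rule. Section 5.2 already has additional tests and extra visits recorded, scheduled tests can be identified from the calendar, and an analysis plan not shown here may report the two apart. The endpoint is also the last of ten secondary endpoints in a descriptive study, and the synopsis list of eight omits it.

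Much of that stands. It limits the weight of the point and shows that the repair needs no new data. It does not remove the point, because item 10 as written sets the test cost against an objective about treating diabetes without saying that the study itself orders much of that testing. Reporting the additional tests alone would not recover usual care either (step 3).

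A reader might infer more than the documents support:
- **That endpoint 10 as a whole mostly returns the schedule.** Medication cost is the first component named and drug choice is left to routine care. Step 4 gives anything from 20% to 80% under its assumptions.
- **That study visits are counted as resource use.** Item 10 does not name visits. They enter only if read into its closing reference to other procedures.
- **That endpoint 6 is affected too.** Fundus and foot examinations, the examples it names, are not on the laboratory list or the flow chart.
- **That differences between hospital tiers or insurance groups must shrink.** A common floor reduces ratios but cancels in absolute differences. Those narrow only if scheduled tests replace routine ones to differing degrees, which the documents do not show. Section 7 names no comparison of resource use between such groups.

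**Conclusion.** The point holds for the diagnostic-test cost component. The protocol sets a floor of 20 follow-up panels per completer (26 with baseline), and item 10 has no rule to separate it. A single total that includes these tests cannot be read as the usual-care pattern that objective 8 seeks.

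To say that the component is in large part induced by the schedule rests on unscheduled panels staying below about 20 per patient in the year and on broadly similar panel costs. Neither is given. The size of the overstatement in money cannot be derived from the protocol, because unit costs, the drug share and the usual-care testing rate are all absent. Medication cost is not fixed by the schedule, though scheduled HbA1c results could influence prescribing. The primary endpoint is untouched.

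**What to change.** In 6.2 item 10:
- Report the cost of protocol-scheduled tests on a separate line from medications, additional routinely ordered tests, extra visits and procedures.
- Give the total with and without the scheduled tests.
- State that the two totals bracket usual-care test use: the first overstates it, and the second understates it because scheduled tests may replace tests that would have been ordered anyway.

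This uses records that section 5.2 already calls for and takes a few sentences in the protocol. The small downside is that usual-care test cost becomes a range.

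A field marking each test as routine or study-only could narrow the range, but it is optional. It asks investigators at about 80 hospitals for a counterfactual judgement on every test, and misclassification could differ by site. If an analysis plan already makes the separation, item 10 needs only a reference to it and the statement on interpretation.
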